#### Safety monitoring

The safety of the experimental medical device will be further monitored by clinical examination of the participants immediately after the ESUS study and by remote follow-up 1 week later. After this period, no adverse events related to the ESUS study will be expected.

Overall safety conditions will be monitored through the occurrence of unanticipated adverse events or serious adverse events. If these situations occur, the reportable adverse events will be communicated to the competent authorities according to current regulation, and the corrective actions will be implemented.

### Outcomes

#### Primary outcome

The presence of cataract is obtained with the ESUS.

Secondary outcomes are as follows:i.Cataract type and severity estimated with ESUS based on the LOCS IIIii.Cataract hardness estimated with ESUS, measured in GPaiii.OPE level estimated with ESUS based on the parameters indicated by the phacoemulsifieriv.Number and severity of ESUS-related adverse events

#### Timelines and methods for outcomes recording

Study status: not yet recruiting

Starting date: October 2022

The total duration of the clinical study will be 15 months, and it will be divided into two phases:First phase: 9 months (6 months for recruitment and 3 months for participant follow-up).Second phase: 6 months (3 months for recruitment and 3 months for participant follow-up).

In the first phase, the cataract type and severity measured with slit lamp/LOCS III and contrast sensitivity will be used to train the algorithms for cataract detection and classification in humans. The surgical records (maximum phacoemulsification energy, phacoemulsification time and surgical complications), number and morphology of endothelial cells (measured by specular microscopy), the presence of macular oedema (assessed by OCT) and postoperative complications will support algorithm development for the estimation of OPE.

In the second phase, the cataract type and severity classification and OPE estimation will be implemented with the ESUS using the algorithms developed/trained in the first phase. The remaining study assessments will be used for preliminary performance evaluations. The methods for algorithm development are described in the “Statistical analysis” section.

### Statistical analysis

#### Feasibility assessment

The feasibility of the ESUS technique will be evaluated based on cataract detectability, cataract classification and OPE estimative performances and on the ESUS safety.

Cataract detectability will be considered suitable if at least 90% of the cases detected through slit lamp observations are identified by the ESUS.

The cataracts classification will be considered suitable if sensitivity levels higher than 90 %, with a maximum significance level of 5%, are reached.

The system efficacy for the OPE will be considered suitable if the prediction accuracy is higher than 90%.

Since the clinical procedure involved in data acquisition with the ESUS is similar to the used in biometry for IOL power calculation, the procedure viability is not object of the study.

The ESUS safety will be considered suitable under two conditions: (i) there are no occurrence of serious adverse event associated with ESUS whose causes cannot be rectified; (ii) the occurrence rate of mild to moderate ESUS-related adverse events is lower than 5%.

The feasibility study will be considered successful if at least the primary objective, detection of the presence of cataracts, and the secondary objective of cataracts classification (type and severity) are reached and if the safety of the ESUS technique is verified.

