Acoustic parameters extracted from ultrasonic waves propagating in cataractous lenses have been widely studied to characterize their structural and biomechanical properties. Several studies have characterized the presence and severity of cataracts using this approach [4, 8–12]. Moreover, studies have used ultrasound for cataract hardness estimation [8, 13–20] since the efficient energy that must be applied to phacoemulsification surgeries is directly related to cataract hardness [17]. Most of these studies were conducted in porcine lenses due to the similarities in their acoustic parameters with human lenses [21].

Preclinical studies were conducted by the research team with two models of cataracts: ex vivo in porcine lenses [8, 20] and in vivo in rat lenses [12]. These studies evaluated several automatic classification methods for cataract hardness and severity based on features extracted from the ultrasonic signals. The results showed a precision, sensitivity and specificity of 99.7% for cataract severity classification, as well as a statistically significant difference in lens hardness for the different cataract severities [12].

The present pilot study protocol aims to evaluate the Eye Scan Ultrasound System (ESUS), which was developed in the preclinical studies [22] and adapted for clinical applications [23] in human lenses in vivo. Because it is a first in human study, and to reduce risks and optimize human and financial resources, a pilot protocol was designed for feasibility assessment of the ESUS in clinical practice. It aims to assess the feasibility of detecting and characterizing human cataracts by ultrasound and the suitability and safety of the technique for use in clinical practice. Related to cataract characterization, the study protocol was designed to evaluate the performance of the experimental medical device ESUS for the automatic classification of cataract type and severity based on the Lens Opacity Classification System III (LOCS III, [24]) and to estimate the optimal phacoemulsification energy (OPE).

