#### Sample size and allocation

In the first phase of the clinical study, forty participants will be included, and the two eyes will be studied. The participants will be equally distributed into four groups (based on slit lamp/LOCS III classification): participants with incipient, moderate and severe cataracts and participants without cataracts will be included as the control group. The second phase will include at least ten participants, and the two eyes will be studied. Safety will be evaluated for all the recruited participants along the first and second phases.

Since this is a protocol for a pilot study, no sample size estimate was performed. The number of eyes expected to be analysed along the study (i.e. 20 per arm) was considered adequate for this study [30]. The statistical power will be determined at the end of the study for statistically significant results.

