#### Cataract type and severity estimation

The automatic classification system will classify the cataract type (nuclear, cortical, or posterior subcapsular) and evaluate the severity.

From the acquired ultrasonic signals, several acoustic parameters in the time and frequency domains will be extracted. Then, more representative parameters will be selected through a principal component analysis and used for automatic classifier training (e.g. support vector machine, Bayes network and random forest). The performance of the different classifiers will be compared. The classification obtained by a trained specialist using the LOCS III will be used as a reference.

In the second study phase, a preliminary evaluation of the automatic classification performance will be conducted using a new dataset. It will be considered suitable if it reaches sensitivity levels higher than 90%, with a maximum significance level of 5%.

All the participants/eyes performing the ESUS study will be included in the analysis.

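### The detection and classification rules take no account of false positives, so a device that calls every eye cataractous meets the primary criterion

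*Protocol article*

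**What the plan says.** All the performance rules stand in the Statistical analysis section of the protocol article.

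- **Detection (primary), under Feasibility assessment:** "Cataract detectability will be considered suitable if at least 90% of the cases detected through slit lamp observations are identified by the ESUS".
- **Classification, same section:** "The cataracts classification will be considered suitable if sensitivity levels higher than 90 %, with a maximum significance level of 5%, are reached". Cataract type and severity estimation repeats this threshold for phase 2.
- **Overall success:** "The feasibility study will be considered successful if at least the primary objective, detection of the presence of cataracts", together with type and severity classification and verified safety, are all achieved.

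Under Sample size and allocation, phase 1 has forty participants in four equal groups: three severities of cataract, and "participants without cataracts will be included as the control group". Phase 2 has at least ten participants, both eyes studied, with no stated division between cataract and control. Safety is assessed in everyone recruited.

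Cataract type and severity estimation lists three cataract types as classifier outputs, plus severity. It does not list absence of cataract as a class.

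Specificity is mentioned once, as a preclinical result in Background: "precision, sensitivity and specificity of 99.7% for cataract severity classification". The one accuracy threshold concerns phacoemulsification energy, which overall success does not require.

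**The concern.** Presence of cataract according to the device is the primary outcome. A rule that looks only at diseased eyes cannot separate a device that reads the ultrasound signal from one that always gives the same answer. Detecting cataract means telling affected from unaffected eyes, and the unaffected half of that comparison is absent from the rule.

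False positives matter for the use the authors have in mind. The Introduction looks towards finding incipient cataract before symptoms in people at high risk, where a wrong positive call is a main error. The protocol recruits cataract-free controls who could answer the question, yet gives them no role in either performance rule. The results are meant to support a larger study, so an uninformative primary criterion would weaken that case.

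**Working it through.** **Inputs (Sample size and allocation; Feasibility assessment)**
- Phase 1: 40 participants, 4 equal groups, 2 eyes each.
- Phase 2: at least 10 participants, 2 eyes each; cataract/control split not stated.
- Detection threshold: 90% of slit-lamp-positive cases.

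**Step 1: the protocol's own figure.** Eyes per group = 40 / 4 × 2 = 20, which agrees with the stated 20 per arm. This gives 20 control eyes and up to 3 × 20 = 60 cataract eyes. Sixty assumes that every cataract participant is affected in both eyes, which the article does not guarantee. With one affected eye each, the number would be 30.

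**Step 2: a device that always answers 'cataract'.**
- Sensitivity = 60/60 = 100% (Clopper-Pearson 95% interval 94.0 to 100%), or 30/30 = 100% at the lower end. Rule met.
- Specificity in control eyes = 0/20 = 0% (0 to 16.8%).
- Accuracy = 60/80 = 75%.
- Youden index = 1 + 0 − 1 = 0, that is, no information.

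**Step 3: a device that calls 95% of eyes positive at random.** The chance of meeting the rule is P(X ≥ 0.9n), X ~ Binomial(n, 0.95):
- n = 60, at least 54 needed: 0.970
- n = 30, at least 27 needed: 0.939
- n = 20 (all phase 2 eyes cataractous), at least 18 needed: 0.924

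**Step 4: phase 2, split assumed because it is not stated.** With 0, 2, 4 or 10 control eyes among 20, the always-positive device has accuracy 20/20 = 100%, 18/20 = 90%, 16/20 = 80% or 10/20 = 50%. Its sensitivity is 100% each time, so the rule sees no difference.

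**Step 5: adding a specificity floor (90% assumed), on 60 cataract and 20 control eyes.** Both at least 54/60 and at least 18/20 are needed.
- Always-positive device: passes with probability 0 instead of 1.
- Random caller at 95%: about 6 × 10⁻²² instead of 0.970.
- Device with true sensitivity and specificity of 0.95: 0.970 × 0.9245 = 0.897.

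**Step 6: can phase 2 controls alone carry a 90% floor?** Two or three control participants give 4 or 6 eyes.
- One error gives 3/4 = 75% or 5/6 = 83%, so the floor allows none.
- With no errors, the exact 95% lower limit is 0.025^(1/4) = 40% or 0.025^(1/6) = 54%.
- A device with true specificity 0.95 makes no error with probability 0.95⁴ = 0.81 or 0.95⁶ = 0.74.
- Pooled with the 20 phase 1 control eyes there are 24 or 26. Two errors are then allowed (22/24 = 91.7%, 24/26 = 92.3%), and that device passes with probability 0.884 or 0.861.

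Steps 3, 5 and 6 treat eyes as independent. Two eyes of one person are correlated, so those probabilities and the intervals are illustrative. The always-positive result does not depend on independence.

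**The case against.** Several stronger readings are tempting, and the article does not support them.

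- **Controls have no role in the verdict.** They do. They supply phase 1 training data, and safety, a condition of overall success, is judged in all recruited participants. Only the detection and classification criteria leave them out.
- **A constant output would make the whole study a success.** It would not. Overall success also needs type and severity classification, which the answer 'cataract' alone does not supply.
- **Training eyes count towards the 90%.** A reader might infer this from "All the participants/eyes performing the ESUS study will be included in the analysis". That sentence more naturally means that no scanned eye is excluded, and it stands in the type and severity subsection. The Abstract, Introduction and Timelines sections assign training to phase 1 and assessment to phase 2. What remains is that the detection rule does not itself name the phase.
- **The classifier will be tuned to over-call.** Nothing says that it is trained to a sensitivity target. It is trained on LOCS III labels, and 90% is an acceptance threshold.

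Two defences deserve an answer. First, if classification sensitivity were computed per class with 'no cataract' as a class, that class's sensitivity would be the specificity. The article does not say this, and it would leave the detection rule unchanged. The 5% significance level is attached to sensitivity and does not help. Second, this is a first-in-human pilot with an avowedly preliminary evaluation. That justifies modest precision. It does not justify a stated pass mark that an uninformative device meets. The choice of agreement statistics or interval methods can be left to a fuller document and is not criticised here.

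**Conclusion.** The concern holds for the two performance rules. As stated, a false positive in a cataract-free eye cannot affect the detection or the classification verdict, and a device that calls every eye cataractous meets the primary criterion with 100% sensitivity and 0% specificity in the 20 phase 1 control eyes. That holds for any number of cataract eyes and for any phase 2 split. The figure of 20 control eyes rests on the stated equal allocation. The phase 2 composition is unknown, so phase 2 may contain no eye on which specificity could be measured.

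The conclusion stops short of overall success, which has two further conditions, and it makes no claim that training data leak into the assessment.

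**What to change.** 1. **Detection:** require both sensitivity of at least 90% in slit-lamp-positive eyes and specificity at or above a prespecified floor in slit-lamp-negative eyes. Ninety per cent is a reasonable default that the sponsor may change. Give confidence intervals that allow for two eyes per participant.
2. **Classification:** state that 'no cataract' is one of the classes when sensitivity is computed.
3. **Phase 2:** reserve some places for controls, and state that the verdict uses phase 2 eyes.
4. **Small numbers of controls:** since 4 to 6 control eyes give a very imprecise specificity, choose one of two routes in advance. Either express the floor as an allowed number of errors among phase 2 control eyes, or make a declared exception for specificity only. Under that exception, phase 2 controls are pooled with out-of-fold predictions for the 20 phase 1 control eyes, with folds split by participant.

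The cost is mainly wording, because controls are already planned and the article reports that recruitment has not begun. A few phase 2 places go to controls, which leaves fewer cataract eyes for sensitivity, and the criterion becomes harder to meet. On the phase 1 numbers, a device with true sensitivity and specificity of 0.95 would pass with probability 0.897 rather than 0.970.

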#### Interim analysis

An interim analysis will be performed between the end of the first phase of the study and the beginning of the second phase of the study.

The sponsor will continuously analyse safety data and will evaluate the results from the interim analysis. Based on the analyses, a consensus between the responsible investigator and the sponsor may end or suspend the study. The Portuguese National Authority for Medicaments and Health Products (INFARMED, I.P.) or the Portuguese National Ethical Committee for Clinical Research (CEIC) may also prematurely end the study.

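### Safety condition (i) can be met for a device configuration in which serious ESUS-associated events occurred, if their causes are judged rectifiable and without any evidence from after a correction

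*Protocol article*

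**What the plan says.** The Feasibility assessment section of the protocol article sets two safety conditions. Condition (i) is that "there are no occurrence of serious adverse event associated with ESUS whose causes cannot be rectified". Condition (ii) is that "the occurrence rate of mild to moderate ESUS-related adverse events is lower than 5" per cent. The same section calls the study successful if cataract detection and classification "are reached and if the safety of the ESUS technique is verified", so the safety verdict is a required component of success.

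Other sections describe what happens to the events themselves:

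- **Outcomes**, secondary outcome iv: "Number and severity of ESUS-related adverse events".
- **Table 1**: adverse events are collected at every visit from the ESUS procedure to the second postoperative follow-up.
- **Safety monitoring**: when unanticipated or serious events occur, "the reportable adverse events will be communicated to the competent authorities according to current regulation, and the corrective actions will be implemented".
- **Interim analysis**: "The sponsor will continuously analyse safety data and will evaluate the results from the interim analysis", and "a consensus between the responsible investigator and the sponsor may end or suspend the study". The national authority and the national ethics committee can also end the study early.
- **Sample size and allocation**: in the first phase "forty participants will be included, and the two eyes will be studied". The second phase adds at least ten participants, and safety is evaluated in everyone recruited.

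**The concern.** A safety criterion for a first-in-human device should answer whether the device as tested caused serious harm. Condition (i) answers a different question: whether the cause of any such harm could be put right. A rectifiable cause suggests that a modified device or procedure might be safe. It does not show that the tested one was, and the rule asks for no data on the modified one.

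The verdict is therefore ordered oddly. A small excess of mild events fails the device, while serious device-associated events can leave the verdict untouched. At stake is the meaning of the safety component in the declared success of the study. A reader told that safety was suitable would not learn from that statement whether serious device-associated events had occurred.

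**Working it through.** The article gives no safety sample size, power or error rate, so there is no figure to reproduce. The check is of the logic of the rule, with some exact binomial arithmetic for scale.

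**Inputs.** Conditions (i) and (ii) come from Feasibility assessment. The numbers come from Sample size and allocation: 40 + 10 = 50 participants (a minimum, since the second phase is at least ten), or 2 × 50 = 100 eyes.

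**Step 1: which events each condition counts.**

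| ESUS-associated event | Condition (i) | Condition (ii) |
|---|---|---|
| Serious, cause not rectifiable | fails | not counted unless also graded mild or moderate |
| Serious, cause rectifiable | passes, any number | not counted unless also graded mild or moderate |
| Non-serious, mild or moderate | not counted | counted |

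The second row is the gap. The number of serious events is not an input to condition (i). It enters condition (ii) only through events also graded mild or moderate.

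**Step 2: what condition (ii) allows.** A rate below 5% permits at most 2 of 50 participants (2/50 = 4%), because 3/50 = 6%. Counted by eye, it permits at most 4 of 100 (4%).

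**Step 3: whether another section closes the gap.** Safety monitoring requires corrective action but does not link the verdict to what is seen afterwards. Sample size and allocation pools all participants over both phases, with no split at a correction. Outcomes records number and severity, but Feasibility assessment does not use the number of serious events. Interim analysis covers ending or suspending the study, not the definition of suitable safety. None of these changes the second row of the table.

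**Step 4: what a clean result after a correction could show.** For zero events in n participants, the exact one-sided 95% upper limit is 1 − 0.05^(1/n).

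- n = 50: 1 − 0.05^(1/50) = 0.058, about 5.8%.
- n = 10: 1 − 0.05^(1/10) = 0.259, about 26%.

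The second figure applies if a correction were made between the phases and only the ten second-phase participants were scanned afterwards.

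**Step 5: illustration only.** Let p be the true risk per participant of a serious ESUS-associated event, and q the share of such events judged rectifiable. The documents give neither. If events are independent and all 50 participants are scanned, the chance of meeting condition (i) is (1 − p(1 − q))^50.

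| p | q = 0 | q = 0.5 | q = 0.8 | q = 1 |
|---|---|---|---|---|
| 1% | 60.5% | 77.8% | 90.5% | 100% |
| 2% | 36.4% | 60.5% | 81.8% | 100% |
| 5% | 7.7% | 28.2% | 60.5% | 100% |
| 10% | 0.5% | 7.7% | 36.4% | 100% |

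At p = 5% the chance of at least one serious event is 1 − 0.95^50 = 92.3%. The q = 1 column is true by construction. The table shows how strongly the verdict can depend on the judgement of rectifiability. The claim itself rests on Steps 1 to 3.

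**The case against.** The other side has several sound points.

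- **The clause has a rationale.** Safety considerations lists hazards such as configuration errors, contamination and electrical leakage, several of them plausibly correctable. Separating correctable faults from inherent harm is defensible in a first-in-human pilot, and insisting on a flat zero-event rule is partly preference. This stands, and it is why the fix leaves a route to a favourable verdict after a correction.
- **Events do not disappear.** One might infer that serious events are dropped from the study. The documents do not support that: they are collected, reported as an outcome and sent to the authorities where reportable, and outside bodies can end the study. Only the verdict is affected.
- **Recurrence would tell.** A repeat event from the same cause after a correction would suggest that the cause had not been rectified, which bears on condition (i). That limits how far an unlimited count could pass in practice. It does not help where the events precede the correction or have different causes, and the rule requires no period of observation afterwards.
- **Definitions may sit in the full protocol.** Who judges rectifiability, and how, is detail that an article may leave out, and no point is made of its absence. The pass/fail rule itself is stated here, however, and a definition of rectified would still leave such events uncounted.
- **The probabilities are weak evidence.** p and q are assumed. A shared device fault would make rectifiability correlated between participants, and the formula ignores suspension of the study. All of this is accepted.
- **The fix may leave few participants.** This is correct, and is why their number and the upper limit must be stated.

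**Conclusion.** The point holds as a fault in a stated criterion. Followed exactly, conditions (i) and (ii) can label ESUS safety suitable although serious device-associated events occurred in the configuration tested, provided their causes are judged rectifiable. No evidence from after the correction is needed. The conclusion rests on the wording alone and on no assumed event rate. The contrast with the limit of 2 in 50 for mild to moderate events shows the imbalance.

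Two further inferences should not be drawn. A reader might suppose that this verdict is the gate to the larger study, but the article says only that the results will support or be used in one and makes nothing conditional on the label. A reader might also blame the nonblinded design. Every participant, controls included, is scanned with ESUS, so there is no unscanned arm against which device safety could be blinded.

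The change is worth making: the safety verdict is required for declared success, and the article gives the study status as not yet recruiting.

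**What to change.** 1. Reword condition (i) so that every serious ESUS-associated event counts against the device configuration or procedure in which it occurred.
2. Keep rectifiability as a reported description of each event, not as a term in the criterion.
3. If a correction is made, report safety separately for participants scanned before and after it.
4. After a correction, allow a verdict of suitable only from participants scanned with the corrected device, stating their number and the exact upper confidence limit for the serious-event risk, so that a clean result in ten people is not read like one in fifty.

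Clinical handling of events and decisions on continuing or suspending the study are unchanged.

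The cost is one reworded criterion, a split of the safety table and, if a correction occurs, an analysis set defined by configuration. The downside is that the safety verdict becomes less favourable after a serious event, and a verdict reached after a correction may rest on few participants.

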### Procedures

The participants’ visit schedule is presented in Table 1, and descriptions of the interventions and assessments are given below.

**Table 1 Tab1:** SPIRIT figure showing the schedule of enrolment, interventions and assessments

	Enrolment	Allocation	Post-allocation	Post-allocation			
Time point (day)	t_1_			t_2_	t_3_	t_4_	t_5_
Enrolment							
Demographic and medical record	✓						
Slit lamp and LOCS III	✓						
Inclusion/exclusion criteria	✓						
Informed consent	✓						
Allocation		✓					
Interventions							
Phacoemulsification surgery^b^					✓		
Assessments							
ESUS			✓				
Contrast sensitivity^a^			✓		✓		
Specular microscopy^b^			✓			✓	
Optical coherence tomography^b^			✓			✓	✓
Surgical and postoperative complications record^b,c^					✓	✓	✓
Safety monitoring^d^			✓	✓			
Adverse events			✓	✓	✓	✓	✓

t_1_, diagnosis, recruitment and ESUS procedure; t_2_, safety assessment (a week after t_1_); t_3_, phacoemulsification surgery; t_4_, 1st follow-up (a week after t_3_); and t_5_, 2nd follow-up (a month after t_3_)

^a^Procedure to be performed alternatively on t_1_ or t_3_

^b^Procedures to be conducted only on cataract group

^c^If both eyes received indication for phacoemulsification surgery, data from both surgeries will be collected

^d^A clinical evaluation will be done immediately after the ESUS study and a remote evaluation 1 week later. The procedures will be performed in both eyes

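### The ESUS safety rule leaves severe but non-serious device-related events out of both its conditions, states no counting unit for its 5% rate, and is a bare observed rate that cannot by itself establish a true rate below 5%

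*Protocol article*

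**What the plan says.** The rule is in the Protocol article, Statistical analysis, Feasibility assessment. Condition (i) is that "there are no occurrence of serious adverse event associated with ESUS whose causes cannot be rectified". Condition (ii) is that "the occurrence rate of mild to moderate ESUS-related adverse events is lower than 5" per cent. The same section makes verified safety one of the requirements for calling the feasibility study successful, next to detection and classification of cataracts.

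Under Outcomes, the fourth secondary outcome is "Number and severity of ESUS-related adverse events", with no restriction to particular grades.

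Under Sample size and allocation, in the first phase "forty participants will be included, and the two eyes will be studied". For the second phase: "The second phase will include at least ten participants, and the two eyes will be studied". On the safety population: "Safety will be evaluated for all the recruited participants along the first and second phases". On the basis for the numbers: "no sample size estimate was performed". Footnote d to Table 1, which describes the safety evaluations, adds: "The procedures will be performed in both eyes".

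**The concern.** Three features of the rule matter, in this order.

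- **Coverage.** Seriousness and severity are different scales. Condition (i) is written on the first and condition (ii) on the second, and together they do not cover every event. Enough mild events can fail the device, while a severe event that does not meet the definition of serious cannot.
- **Unit.** The rate could be counted per participant, eye, examination or event. With two eyes per person the choice can change the verdict. The study is nonblinded and the sponsor reviews safety data continuously, so a unit that is not fixed beforehand could be chosen with the data in view.
- **Strength of the conclusion.** The rule compares an observed proportion with 5%, but the success criterion speaks of safety being verified. A reader may take a pass as evidence that the true rate is below 5%.

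This is a first-in-human study of a probe coupled to the cornea, and its results are meant to support a larger study. The safety statement will be carried forward.

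**Working it through.** **Inputs.** Phase one has 40 participants and phase two at least 10, two eyes each (Sample size and allocation). The planned minimum is therefore 40 + 10 = 50 participants and 50 × 2 = 100 eyes. The threshold is an observed rate below 5%. The article gives no confidence level for the safety rule; 95%, one-sided and two-sided, is assumed here.

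**The plan's own figure.** The only size figure is 20 eyes per arm: 40 participants / 4 groups × 2 eyes = 20. It reproduces from phase one alone. It is a count, and has no link to the 5% rule.

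**Step 1: which ESUS-related events the rule covers.**

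| Event | Condition (i) | Condition (ii) |
|---|---|---|
| Serious, cause cannot be rectified | counts | only if mild or moderate |
| Serious, cause can be rectified | exempted by the wording | only if mild or moderate |
| Not serious, mild or moderate | no | counts |
| Not serious, severe | no | no |

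The last row is the gap. Such an event is in the recorded outcome but has no route into the decision.

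**Step 2: the unit.** Suppose that each affected participant has one affected eye.

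- 2 affected: 2/50 = 4% (pass); 2/100 = 2% (pass).
- 3 affected: 3/50 = 6% (fail); 3/100 = 3% (pass).
- 4 affected: 4/50 = 8% (fail); 4/100 = 4% (pass).

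Per participant the rule passes with 0 to 2 of 50. Per eye it passes with 0 to 4 of 100, since 5/100 is exactly 5% and not below it.

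**Step 3: what a pass says about the true rate.** With zero events in n, the exact upper limit is 1 − a^(1/n), where a = 0.05 (one-sided) or 0.025 (two-sided). With x > 0 events it is the Clopper-Pearson limit.

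- 0/50: 1 − 0.05^(1/50) = 5.8%; 1 − 0.025^(1/50) = 7.1%.
- 2/50, the worst passing result: 12.1% one-sided, 13.7% two-sided.
- Smallest n for which zero events excludes 5%: 59 one-sided, 72 two-sided.
- Chance of a pass per participant, P(X ≤ 2 | n = 50): 0.54 at a true rate of 5%, 0.23 at 8%, 0.11 at 10%.

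**Step 4: how far step 3 depends on its assumptions.**

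- Eye as unit, eyes independent: 0/100 gives 3.0% one-sided and 3.6% two-sided.
- Eye as unit, within-person correlation ρ (assumed), effective n = 100/(1 + ρ): at ρ = 0.69 the effective n is 59.2 and the one-sided limit 4.9%; at ρ = 0.75 the limit is 5.1%; at ρ = 1 it returns to 5.8%.
- Participant as unit, one-sided 90%: 1 − 0.10^(1/50) = 4.5%.

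**The case against.** *The study does not ignore severe events.* This stands. Every grade is recorded, unanticipated effects are a ground for withdrawal, unanticipated or serious events are monitored, and the sponsor can agree with the investigator to suspend or end the study. A reader might infer that a severe event would go unnoticed; the article does not support that. These safeguards do not alter the two-part success rule, however, and the gap is confined to that rule.

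*The wording may be loose, with serious meant as the step above moderate.* This is possible, and grading details may sit in the full protocol. But the article states the rule in full, and on its words the severe non-serious class is not placed in either condition.

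*The safety population is defined in participants.* This points to participants as denominator and makes the per-participant reading the more natural one. It does not settle the numerator: events, affected eyes and affected participants all remain open.

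*Fifty participants cannot show a rate below 5%.* A reader might infer this from step 3, but it goes too far. The rule asks only for an observed rate, which 0 to 2 of 50 meets. Fifty is a minimum. The statement also needs the participant as unit and a 95% bound, neither of which the article sets; step 4 shows it failing under other choices.

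*A pilot need not exclude 5%.* Agreed. A simple observed threshold is a reasonable progression criterion, and verified may mean no more than that the two conditions are met. What follows is that the result should be described in those terms, not that the sample is too small.

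**Conclusion.** The concern holds for the decision rule, and a correction is warranted before recruitment.

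- The coverage gap follows from the text alone and needs no assumption beyond reading serious and severe as distinct terms.
- The missing unit can reverse the verdict: at 50 participants and 100 eyes, three or four participants with one affected eye each fail per participant (6% or 8%) and pass per eye (3% or 4%).
- A pass does not establish that the true rate is below 5%. Per participant at the minimum of 50, with an assumed 95% level, the upper limit is 5.8% or 7.1% with no events at all, and 12.1% or 13.7% with two.

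The third part concerns how the result is worded. It is not a finding that the pilot is undersized.

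**What to change.** Restate condition (ii) as follows: among all participants with at least one ESUS acquisition, the proportion with at least one ESUS-related adverse event of any severity, in either eye, is below 5%. In addition:

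- Report severe events separately by grade. Pooling all grades under one limit would otherwise let a small number of severe events pass without comment.
- Report the proportion with its exact 95% confidence interval, and per-eye counts as a supplement.
- Describe the 5% as a descriptive progression criterion for this pilot, and word the success statement so that it does not read as verification that the true rate is below 5%.
- Do not fix the limit as a count out of 50. Phase two may exceed ten participants, and the permitted count moves with n: three events give 3/50 = 6% (fail) but 3/61 = 4.9% (pass).

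The cost is a few sentences, with no added participants or visits. The rule becomes slightly stricter, because severe events now count, and the safety conclusion becomes more modest. The change does not sharpen the observed-rate criterion: at 50 participants, a true rate of 8% for the events counted would still pass 23% of the time. That is why the interval has to be reported beside the verdict.
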